### **Protection against Risk**

**A.** Patients will be protected against potential risks as follows:

**1. Psychological Distress:** Because we will be administering a questionnaire that measures the presence of depression, we will take several steps to ensure the safety of all research participants. RAs will be trained by the PI to identify patients who meet criteria for depression on the PHQ-9. Subjects' who screen positive for depression will be notified during the visit and verbally instructed to seek care from their primary health care provider (PCP). They will also be given the 24-hour MUSC crisis psychiatry telephone service and told to call if they experience acute worsening of symptoms before they can be seen by their PCP.

**2. Venipuncture (blood drawing):** To reduce the risks of discomfort and bruising, venipuncture will be performed by trained personnel. To reduce the risk of fainting, blood will be drawn while subjects are in a seated position. The amount of blood that will be drawn, approximately 10cc, is not considered to pose a health risk for most adults. .

**3. Blood Pressure Measurement:** To lessen any associated risks, blood pressure measurements will be performed only by trained personnel utilizing a standardized protocol. Subjects with elevated blood pressure will be advised to contact their primary care provider. Those with potentially life threatening blood pressure readings will be sent to a local emergency room for treatment.

**4. Administration of Research Questionnaires:** Some participants might be offended by detailed questions about emotional or physical health status and impairment, and healthcare utilization. All participants will be informed at the outset that they may terminate participation at any point. Our past research suggests that data

collection using these measures can be conducted without undue psychological distress or exacerbation of symptoms among study participants.

**5. Unknown risks:** Subject participation in research may have other unknown risks. The researchers will advise subjects if they learn of emerging information that might alter subjects' decisions to participate in this study.

**B.** Subjects requiring medical or other professional intervention for study-related events will be provided with appropriate and timely medical guidance by the designated medical monitor ([name] – board certified internist). [name] will have oversight on medical risks and will review all adverse events and report them to the IRB in accordance with the MUSC IRB Adverse Event Reporting Policy. The results of subjects' clinical assessments will be available within a few days of their study visit. [name] will review and advise subjects of these results by phone and, at their request; will also advise their personal physician of the results.

**C.** To protect against the potential risk of loss of confidentiality and/or breach of privacy, data will be compiled using codes in lieu of personal identifiers. Access to study data will be limited to research personnel. Development of and security oversight for the electronic database for this study will be performed by the study statistician. Paper documents pertaining to this study will be stored in locked file cabinets and electronic data will be entered into secure, password-protected databases developed for this study by the research assistants. The PI will perform periodic review of the data entry process to ensure accuracy of recording. When study results are published or presented, only aggregate reports of the results will be used and participants' identity will not be revealed. A file of name, contact address, telephone number, and other research identification numbers will be stored separately on paper and on computer, for purposes of audit by the sponsor (NIH) and MUSC IRB, if necessary.

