### **Data Collection Strategy**

**Personnel:** Two half-time masters-level trained diabetes educators (DEs) will deliver the interventions; one full-time research assistant (RA) will conduct screening, consent, enrollment procedures, and questionnaire administration; a half-time data entry clerk (DC) will be responsible for data entry; and a part-time masters-level statistician will be responsible for data management (DM). Each potentially eligible patient will be asked to report for a screening visit. At this visit, the following will be collected: basic demographic information, screening information, and a blood sample for a screening hemoglobin A1c (HbA1c) value. Basic demographic information will be collected to compare those screened to those randomized. Individuals who have a screening HbA1c of  $\geq 8$  will be asked to return within two weeks for a baseline visit. At the baseline visit, a full battery of questionnaires will be administered, and individuals will be randomized. All individuals randomized will have follow-up visits at 3 months, where survey questionnaires will be administered, and blood collected for HbA1c. Blood pressure will also be measured at the baseline and 3 months follow-up visit.

**Primary Outcome Measure: HbA1c:** About 10cc of blood will be drawn by trained phlebotomists and sent to the lab for HbA1c.

**Secondary Outcome Measures: Blood Pressure:** Blood pressure readings will be obtained using automated BP monitors (OMRON IntelliSense™ HEM-907XL). The device will be programmed to take 3 readings at 2 minute intervals, and give an average of the 3 BP readings. **Resource Utilization & Cost:** Previously validated questions on resource utilization will be administered. The questionnaires are 1 page long and capture information on hospitalizations, physician/professional visits, and medications. **Quality of Life:** The SF-12 (Ware 1996) is a valid and reliable instrument to measure functional status. The SF-12 items reproduce at least 90% of the variance in PCS-36 and MCS-36 scores.

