**Covariates: Demographics:** Previously validated items from the National Health Interview Survey will be used to capture demographic characteristics. **Social support:** The Medical Outcomes Study (MOS) Social Support Survey (Sherbourne & Stewart 1991) will be used to measure social support. The total scale ( $\alpha=0.97$ ) has high internal consistency, good criterion and discriminant validity, and one-year test-retest reliability (0.72 to 0.76). **Health Literacy:** This will be assessed by the abbreviated version of the Test of Functional Health Literacy in Adults (S-TOFHLA) (Baker et al, 1999). The S-TOFHLA has a 0.80 correlation with the Rapid Estimate of Adult Literacy in Medicine (REALM). **Depression:** The PHQ-9 is a brief questionnaire that scores each of the 9 DSM-IV criteria for depression as "0" (not at all) to "3" (nearly every day). PHQ-9 score  $> \text{or} = 10$  have a sensitivity of 88% and a specificity of 88% for major depression (Kroenke 2001). **Medical Comorbidity:** The

patient's history of medical comorbidity will be documented using Chronic Health Conditions previously validated items from the Behavioral Risk Factor Surveillance System (BRFSS, 2010). **Diabetes Fatalism:** This will be measured with the 12-item Diabetes Fatalism Scales (DFS) (Egede 2009), a valid and reliable measure of diabetes fatalism ( $\alpha=.804$ ) that is associated with self-care problems, poor glycemic control, and decreased quality of life.

**Patient Randomization:** A permuted block randomization method will be used to assign subjects to one of the three intervention groups 1) High Frequency, 2) Moderate Frequency, and 3) Low Frequency. Block size will be varied to minimize the likelihood that the blind will be broken. The randomization will be stratified by baseline HbA1c levels (8-10% vs. >10%). Using REDCap, RAs will collect eligibility information and enter the information into the study database via the secured study website. Once eligibility is confirmed, the computer will generate the intervention assignment based on the pre-programmed randomization scheme. All subjects who are randomized will be entered into the study database and analyzed according to CONSORT guidelines (Altman 2001).

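### The PHQ-9 safety rule gives every positive screen the same routine response and has no urgent tier with same-visit clinician contact

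*Protocol*

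**What the plan says.** Psychological distress is listed under Potential Risks, which refers the reader to the protection section for how it is minimised. There, item A.1 (Psychological Distress) notes that the trial administers a depression questionnaire and promises that "we will take several steps to ensure the safety of all research participants". The steps are:

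- **Trigger:** "RAs will be trained by the PI to identify patients who meet criteria for depression on the PHQ-9".
- **Response at the visit:** participants "who screen positive for depression will be notified during the visit and verbally instructed to seek care from their primary health care provider".
- **Safety net:** the same participants receive a 24-hour crisis psychiatry telephone service and are "told to call if they experience acute worsening of symptoms before they can be seen by their PCP".

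Item A.3 (Blood Pressure Measurement) advises participants with elevated pressure to contact their primary care provider, and then adds: "Those with potentially life threatening blood pressure readings will be sent to a local emergency room for treatment".

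Paragraph B of the same section makes two general provisions. First, "Subjects requiring medical or other professional intervention for study-related events will be provided with appropriate and timely medical guidance" from the medical monitor. Second, results of clinical assessments become available within a few days; the monitor reviews them, informs the participant by telephone and, if the participant asks, informs the personal physician.

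Under Data Collection Strategy, "one full-time research assistant (RA) will conduct screening, consent, enrollment procedures, and questionnaire administration". Among the covariates listed later, the PHQ-9 is described as an instrument that "scores each of the 9 DSM-IV criteria for depression as" 0 to 3. A total of 10 or more is mentioned there only with its sensitivity and specificity for major depression.

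**The concern.** A.1 has one trigger and one response. A participant whose answers just meet the criteria and one whose answers suggest acute danger are handled alike: told of the result, advised to see their own doctor, and given a number to ring if matters get worse. The instruction to call is tied to later worsening, so it does not address someone who is already at acute risk when the questionnaire is completed.

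The trial itself generates this information, in the presence of a research assistant who is not described as a clinician. If that assistant follows A.1 as written, no clinician hears of the answers that day, however severe they are. The possible harm to an individual is serious, even if it is rare.

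**Working it through.** No arithmetic applies, because the protocol states no figure that bears on this rule. The check is to compare the two response rules and then look for another provision that closes the gap.

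| | A.1, PHQ-9 | A.3, blood pressure |
|---|---|---|
| Routine trigger | Meets criteria for depression | Elevated reading |
| Routine response | Notify, advise primary care, give crisis number | Advise primary care |
| Urgent trigger | None stated | Potentially life-threatening reading |
| Urgent response | None stated | Sent to emergency room |

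A.1 therefore has one tier and A.3 has two. In its routine tier A.1 offers slightly more than A.3, because of the crisis line. What it lacks is the second tier.

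Other provisions that might supply it:

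1. **Paragraph B, guidance for study-related events.** It names no PHQ-9 result and does not tell the research assistant when to call the monitor.
2. **Paragraph B, review of clinical assessments.** A physician looks at results and telephones the participant, but within days, not at the visit. The text does not say whether a questionnaire counts as a clinical assessment. The personal physician is informed only on request.
3. **Crisis line.** The participant has to make the call, and only participants who screen positive receive the number.
4. **Exclusion of active psychosis or acute mental disorder.** This is an entry criterion. No PHQ-9 answer or score is linked to it, and it sets out no response to one.
5. **Data and Safety Monitoring Plan.** The committee meets quarterly and as necessary by telephone. It oversees the study and does not respond at a visit.

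None of the five gives same-visit clinician contact triggered by a PHQ-9 result. Items 2 and 3 reduce the gap without closing it.

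**The case against.** The strongest case on the other side has four parts.

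**Different hazards may have different rules.** A blood pressure reading is a physiological measurement and the PHQ-9 is a screen, so one tier against two is not a contradiction. This stands. A.3 serves here only to show that the protocol already uses an urgent tier where it foresees acute danger.

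**Follow-up does not rest wholly with the participant.** A reader might infer from A.1 alone that no clinician would ever learn of the answers. The documents do not support that, because paragraph B provides for physician review and a telephone call within a few days, and this may extend to the PHQ-9. The gap holds for the day of the visit, which is when an acute answer needs action.

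**The self-harm content comes from outside the protocol.** The protocol says that nine criteria are scored and lists none of them. This also stands. That the PHQ-9 contains a self-harm item is an assumption about the instrument. The main point does not need it: whatever the items ask, the most severe positive screen gets the same response as the mildest.

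**The research assistant's training may go further.** It may, and nothing in A.1 forbids a call to the monitor. But the scope that A.1 gives to that training is recognising patients who meet the depression criteria, and a participant-protection rule should not depend on instructions that it does not mention.

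**Conclusion.** The point holds, at minor severity. A.1 gives every positive PHQ-9 screen one routine response and states no urgent tier with clinician contact before the participant leaves. Paragraph B mitigates this in part, later and without a link to the PHQ-9. No endpoint, analysis or sample-size figure is affected.

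Two further inferences are tempting and should not be drawn:

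- **A range of total scores that would receive no action.** This needs a cut-off. A.1 gives none, and the value of 10 appears elsewhere only as an accuracy property. It is a fair concern that a worrying single answer could sit below whatever threshold is used, but it rests on the assumption about the self-harm item and cannot be put in numbers from the protocol.
- **A number of the 60 participants affected.** The protocol gives no frequency of such answers. It also does not say whether the PHQ-9 is repeated at 3 months; it mentions only survey questionnaires at that visit.

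**What to change.** Add one sentence to A.1:

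> *Before the participant leaves, the RA will check the PHQ-9 answers; any answer indicating possible self-harm, whatever the total score, or any other sign of acute risk, will be passed the same day to the medical monitor, who decides the clinical action.*

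Keep the primary care advice and the crisis line as the routine tier.

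The questionnaire, the research assistant, the training and the medical monitor are already in the plan, so the cost is this sentence and a short addition to the training. There are two downsides. The monitor or a delegate must be reachable on visit days, which the protocol does not currently state. Some calls will also concern answers that turn out to need no action.

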## Data Analysis

### Design/Analysis Issues

Analysis sets. The intent-to-treat (ITT) sample, comprising all randomized patients, will be used for the primary analyses. The per protocol/completer sample will comprise subjects who were compliant with protocol requirements and for whom all required measurements over 3-months of follow-up have been made. Analyses will be carried out separately for ITT and per protocol samples to test sensitivity of conclusions to drop-outs/nonadherence. If differences are present between the per protocol and ITT analysis sets, the characteristics of the two analysis populations will be examined to aid in explaining any discrepancies.

**Analysis Plan for Primary Aim (Efficacy):** To test the efficacy of three financial incentive structures in combination with technology intensified diabetes education and skills training intervention on HbA1c levels in AAs with T2DM. Preliminary analyses will be conducted to assess the similarity of the treatment arms based on collected variables. Univariate descriptive statistics and frequency distributions will be calculated, as appropriate for all variables along with two-sided 95% confidence intervals when appropriate. Study discontinuation (attrition) rates will be estimated for each group. The preliminary analyses will describe the pre-specified covariates as well as identify potential confounding (prognostic) variables to be used as covariates in subsequent secondary analyses. Covariates to be examined in the preliminary analyses and potentially used in secondary analyses include age, sex, income, health literacy, social support, depression, and comorbidity. The primary framework for analysis is paired t-test. Change in HbA1c from baseline to 3-months (dependent variable) will be examined in each treatment arm (high, moderate and low frequency of financial incentives) using a type I error rate of 0.05.

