### Analysis Plan for Secondary Aims:

1. To test the efficacy of three financial incentive structures in combination with technology intensified diabetes education and skills training intervention on blood pressure and quality of life in AAs with T2DM.

2. To test the efficacy of three financial incentive structures in combination with technology intensified diabetes education and skills training intervention on diabetes knowledge and self-care behaviors (medication adherence, diet, exercise).

Similar to the primary analysis, paired t-test will be used to evaluate change in BP, QOL, knowledge and self-care variables from baseline to 3-months (dependent variables) within each treatment arm (high, moderate and low frequency of financial incentives) using a type I error rate of 0.05.

**Analysis Plan for Exploratory Analyses.** Exploratory analyses to examine frequency of session attendance, frequency of uploads and average weekly glucose within the three different financial incentive structures. Univariate descriptive statistics and frequency distributions will be calculated, as appropriate for all variables along with two-sided 95% confidence intervals when appropriate.

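### Within-arm change in HbA1c and blood pressure counts any drug change during the 3 months as incentive efficacy, and no stated analysis uses the medication data

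*Protocol*

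**What the plan says.** **Who enters.** The inclusion criteria require a screening HbA1c of 8% or more and current treatment with an oral diabetes drug or insulin.

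**Feedback.** Protection against Risk, part B, says that results of clinical assessments "will be available within a few days of their study visit". The medical monitor then "will review and advise subjects of these results by phone and, at their request; will also advise their personal physician of the results". Part A of the same section adds for blood pressure: "Subjects with elevated blood pressure will be advised to contact their primary care provider".

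**Efficacy analysis.** Under Design/Analysis Issues: "The primary framework for analysis is paired t-test". It continues: "Change in HbA1c from baseline to 3-months (dependent variable) will be examined in each treatment arm". Blood pressure is handled the same way under the secondary aims, where "paired t-test will be used to evaluate change in BP, QOL, knowledge and self-care variables from baseline to 3-months".

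**Medication data.** Under Data Collection Strategy, the resource-utilization questionnaires "capture information on hospitalizations, physician/professional visits, and medications". The candidate covariates for secondary analyses "include age, sex, income, health literacy, social support, depression, and comorbidity". The only sensitivity comparison named is intent-to-treat against per protocol. No section says how a change of glucose-lowering or antihypertensive drugs is treated in the analysis.

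**The concern.** The study recruits people whose diabetes is poorly controlled on treatment and tells them their results. It may also tell their physician, and it advises those with raised blood pressure to seek care. Each of these steps may lead to a treatment review early in a 3-month follow-up. The drugs under review act directly on the primary endpoint and on one secondary endpoint.

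That would matter less if efficacy were judged by comparing arms, because nothing in the protocol makes the feedback depend on the arm. But the stated test looks at each arm alone. A fall in HbA1c after a drug was added enters the arm mean in full and is read as efficacy of the incentive structure. This mechanism is separate from regression to the mean. Neither the paired test nor the intent-to-treat versus per-protocol comparison would reveal it.

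**Working it through.** **Inputs from the protocol (Sample Size and Power).** 18 per arm, 20 after inflation; two-sided alpha 0.05; HbA1c SD 1.5; correlation between visits at most 0.5; target change 1.0 point within an arm.

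**The plan's own figure.** 18 per arm for 85% power at 1.0 SD reproduces (85.1%) with the normal-approximation formula for two independent means. Allowing 10% gives 18/0.9 = 20. That formula is not the planned paired test, which is a separate matter; the present point does not rest on it.

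**Assumptions, not in the protocol.** The share of an arm whose drugs are intensified, and the mean HbA1c fall that results.

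**Shift in the arm mean** = share × effect.
- Low end: 0.20 × 0.5 = 0.1 point.
- High end: 0.40 × 1.5 = 0.6 point.
- Against the 1.0-point target, this is 10% to 60%.

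**Effect on the paired test when the incentives do nothing.** SD of change = 1.5 × sqrt(2 × (1 − 0.5)) = 1.5. The rejection probability comes from the noncentral t with n − 1 degrees of freedom and noncentrality shift/1.5 × sqrt(n). For a shift of 0.30 and n = 20, the noncentrality is 0.30/1.5 × 4.47 = 0.89.

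| Share | Effect (points) | Shift (points) | Rejection, n = 20 | Rejection, n = 18 |
|---|---|---|---|---|
| 0 | – | 0 | 5.0% | 5.0% |
| 10% | 0.5 | 0.05 | 5.2% | 5.2% |
| 20% | 0.5 | 0.10 | 5.9% | 5.8% |
| 20% | 1.0 | 0.20 | 8.8% | 8.3% |
| 30% | 1.0 | 0.30 | 13.6% | 12.6% |
| 50% | 1.0 | 0.50 | 29.4% | 26.6% |

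The 50% row lies outside the 20% to 40% range and shows only where the curve leads. A correlation below 0.5 makes the SD of change larger and these increases smaller.

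**What a between-arm comparison would offer.** If feedback shifts every arm by about the same amount, the shift drops out of the difference. The standard error for two arms of 20 is 1.5 × sqrt(2/20) = 0.47 point, so the 95% half-width is about 1.96 × 0.47 = 0.93 point. The comparison would be imprecise, but the common shift would not bias it.

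**The case against.** **The SAP may deal with it.** Drug-change tables and sensitivity analyses often sit in a SAP, which is not at hand, and the covariate list may not be exhaustive. This has force: absence of a table from the protocol would not be a finding. What stands is that the protocol itself fixes uncontrolled within-arm change as the test of efficacy, and that rule misattributes drug-driven falls.

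**Medication is not ignored.** Resource Utilization & Cost, which includes medications, is listed among the secondary outcome measures. So it would be wrong to infer that medication is no outcome at all. The narrower statement holds: no analysis of it is stated, and drug change is not singled out.

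**Drug change may be part of the effect.** The sessions aim at activation and empowerment, and subjects are paid for a lower HbA1c. Some may seek a treatment review for that reason. This stands. It rules out treating drug change as pure contamination, adjusting for it as an ordinary covariate, or letting an analysis without intensified patients settle the question. Those patients may be the poorest responders, so leaving them out could also inflate the apparent effect.

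**Stronger readings that the text does not support.**
- A reader might infer that study feedback will cause intensification. The protocol gives no rate of drug change and only makes the route possible.
- A reader might infer that physicians routinely receive HbA1c results at baseline. They are told only if the subject asks, and the text refers to clinical assessments and study visits without naming HbA1c or baseline.
- A reader might infer that chance imbalance in drug changes would bias a comparison of arms. Under randomisation it is ordinary variance and belongs in the standard error; no such comparison is planned in any case.

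**Conclusion.** The point holds as a limit on attribution. As planned, within-arm change in HbA1c and blood pressure mixes incentives, education and any drug changes, and the protocol labels the sum as efficacy of the incentive structure.

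The size is unknown. Under the assumed shares and effects, drugs alone would move the arm mean by 0.1 to 0.6 point against a 1.0-point target. With few or small changes the effect is negligible: 5.2% rejection instead of 5% in the mildest case shown. The HbA1c figures rest wholly on those assumptions, and no figure is offered for blood pressure.

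The underlying weakness is the uncontrolled within-arm test; drug change is one route by which it can mislead. The correction is cheap and worth making before enrolment, because changes not recorded at both visits may be hard to reconstruct.

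**What to change.** 1. **Data Collection Strategy:** state that the medication items are completed at baseline and at 3 months, and that they record any start, stop or dose change of glucose-lowering and antihypertensive drugs. The protocol does not say that the present questionnaire captures this.
2. **Primary and secondary analysis plans:** report these changes by arm beside the HbA1c and blood pressure results.
3. **Interpretation:** state that within-arm change reflects incentives plus education plus any drug changes and is not by itself evidence of incentive efficacy. Rest attribution to incentive structure on a comparison between the randomised arms, where feedback common to all arms largely cancels. Report it as an estimate with its confidence interval. All three arms receive incentives and education, so this comparison speaks to the structure of incentives, not to the whole package.
4. **Analysis without intensified patients:** show it, if at all, as exploratory only. Drug change happens after randomisation and may lie on the incentive pathway, so this analysis must not decide the conclusion.

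Feedback, referral and clinical care stay as they are; nothing here restricts treatment. The cost is a few questionnaire fields, one table and some protocol wording. The downside is an imprecise between-arm estimate with 20 per arm.
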